## Abstract

**Introduction:**

Frailty has become a worldwide health burden that has a large influence on public health and clinical practice. The incidence of frailty is anticipated to increase as the ageing population increases. Myocardial injury after noncardiac surgery (MINS) is associated with short-term and long-term mortality. However, the incidence of MINS in frail geriatric patients is unknown.

**Methods and analysis:**

This prospective, multicentre, real-world observational cohort study will be conducted at 18 designated centres in China from January 2023 to December 2024, with an anticipated sample size of 856 patients aged 65 years and older who are scheduled to undergo noncardiac surgery. The primary outcome will be the incidence of MINS. MINS is defined as a fourth-generation plasma cardiac troponin T (cTnT) concentration ≥ 0.03 ng/mL exhibited at least once within 30 days after surgery, with or without symptoms of myocardial ischaemia. All data will be collected via electronic data acquisition.

**Discussion:**

This study will explore the incidence of MINS in frail patients. The characteristics, predictive factors and 30-day outcomes of MINS in frail patients will be further investigated to lay the foundation for identifying clinical interventions.

**Clinical trial registration:**

https://beta.clinicaltrials.gov/study/NCT05635877, NCT05635877.

**Supplementary Information:**

The online version contains supplementary material available at 10.1186/s12877-024-04847-z.

## Introduction

The ageing population is quickly increasing worldwide, with the number of people aged 65 years and older expected to reach 2 billion by 2050 [1, 2]. The number of geriatric people undergoing surgery over the past 20 years has increased faster than the ageing of the population [3], which has profound implications for the planning and delivery of health and social care. Clinical frailty is the most troubling manifestation of ageing; it is described as a state of increased vulnerability to poor resolution of homeostasis after a stressful event and is the result of a cumulative decline in multiple physiological systems over a lifetime [1, 2]. Many studies have described the prevalence of frailty, and different surgical specialties have different prevalences of frailty. In patients receiving elective orthopaedic surgery, the prevalence of frailty was 23%, whereas in patients undergoing emergency hip fracture surgery, it was 53% [4, 5]. Taking cancer surgery into account, studies have reported that the prevalence of frailty is 25% in patients who undergo elective cystectomy and 39% in patients who undergo emergency general surgery, with the basal lesion usually being a tumour [6, 7]. In vascular surgery, the risk of aortic aneurysm and peripheral artery disease increases with age, and an estimated 52% of patients undergoing elective vascular surgery are frail [8]. Research on rehabilitation and related outcomes has focused on frail geriatric patients during the perioperative period. Frailty is related to adverse perioperative outcomes [9, 10].

In addition to the underlying conditions of sepsis, pulmonary embolism and arrhythmias, MINS is defined as an increase in cardiac troponin (cTn) during noncardiac surgery or within 30 days, with or without ischaemia-related symptoms and signs or myocardial ischaemic changes (with or without necrosis) [11]. Myocardial injury and infarction are considered the leading causes of death after surgery and account for 25% of all postoperative mortalities [12, 13]; ischaemic myocardial injury occurring after surgery but not meeting the criteria for myocardial infarction is more common [14, 15].

Frail populations often have a greater incidence of subclinical changes in cardiac structure and function, which are considered risk factors for the development of cardiovascular diseases (such as hypertension, heart failure and ischaemic heart disease) [16–19]. Many studies have focused on the development of MINS during the perioperative period, and retrospective studies involving adults aged 45 years and older are common. There is currently no pertinent research on the features, risk factors, or 30-day outcomes of MINS in frail geriatric patients. It is urgent to preoperatively assess the comprehensive health status of frail geriatric patients and to reverse or alleviate frailty as soon as possible [20]. Therefore, the main objective of this study will be to investigate the relationship between preoperative frailty and MINS in geriatric patients.

## Methods and analysis

### Study design

This prospective, multicentre, real-world observational cohort trial has been registered with clinicaltrials.gov (version no. YXLL-KY-2022 (089), October 24, 2022) following approval from the First Affiliated Hospital of Shandong First Medical University’s Ethics Committee (NCT05635877). The study will be performed in accordance with the guidelines of good clinical practice and the Declaration of Helsinki [21, 22]. Moreover, this investigation will comply with the standard protocol Item: Intervention Trial Statement Recommendation (SPIRIT) [23].

The trial is being conducted at 18 centres across China (Table 1). The investigation officially began in January 2023, and it is scheduled to be finished in December 2024. The actual start date of the study is January 2023, and the expected completion date is December 2024. There will be a total of 856 participants, of whom 713 will be placed in the non-frailty group and 143 in the frailty group. The study design is shown in Fig. 1.

**Table 1 Tab1:** Trial centres

Centre	Centre
The First Affiliated Hospital of Shandong First Medical University	Shandong Provincial Hospital Affiliated to Shandong First Medical University
Qilu Hospital of Shandong University	Qilu Hospital of Shandong University (Qingdao)
Affiliated Hospital of Qingdao University	Second Hospital of Shandong University
Chinese PLA 960th Hospital	Qingdao Municipal Hospital
Weihai Municipal Hospital	Liaocheng People’s Hospital
Affiliated Hospital of Jining Medical College	Linyi People’s Hospital
Zibo Central Hospital	Yantai Yuhuangding Hospital
Yantai Affiliated Hospital of Binzhou Medical College	Weifang People’s Hospital
Jining First People’s Hospital	Affiliated Hospital of Weifang Medical College

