### Sample size calculation

In this study, the incidence of MINS will be the primary outcome. According to the literature review and pre-experimental results, the incidence of frailty is estimated to be 20%, with a MINS incidence of 15% in the frailty group and 5% in the non-frailty group. A bilateral α = 0.05 will be used with a 90% confidence interval. The sample sizes of the non-frailty and frailty groups have been calculated using the PASS 15.0 program; 570 patients will be included in the non-frailty group, and 114 patients will be included in the frailty group. Considering that the estimated proportion of patients withdrawn or lost to follow-up is 20%, 713 patients will be included in the non-frailty group, and 143 patients will be included in the frailty group; in total, 856 subjects will be included in the study.

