### Sampling

To reflect the seasonal, weekly and daily distributions of the number of surgical cases, patients will be randomly selected according to the methods in the previous study. Each centre is numbered from 0 to 18 in turn, and a computer will be used to generate a series of random numbers. The mantissa corresponds to each centre. At each centre, data will be collected every week or every day. Recruitment should meet two conditions: (1) Patients should be recruited from at least 1–2 centres every day during the study period. (2) For centres with a sample size greater than 20, the interval between two sampling days should be at least 15 days.

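### The fixed split of 713 non-frail and 143 frail patients is not what random sampling delivers at the plan's own 20% frailty, and the protocol does not say which gives way

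*Protocol article*

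**What the plan says.** Under Study design, the protocol article gives a total of 856 participants, "of whom 713 will be placed in the non-frailty group and 143 in the frailty group". Sample size calculation derives these counts: "570 patients will be included in the non-frailty group, and 114 patients will be included in the frailty group", then raised for 20% withdrawal or loss. The same section states that "the incidence of frailty is estimated to be 20" per cent.

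The Exposure section names preoperative frailty as the exposure, and Study implementation has it measured with the modified frailty index. It is observed, not assigned.

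Sampling describes how patients enter: "To reflect the seasonal, weekly and daily distributions of the number of surgical cases, patients will be randomly selected". The two recruitment conditions that follow concern centres and the spacing of sampling days. Neither refers to frailty status.

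No section closes a group when its count is reached, and none says that the counts are only expected values.

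**The concern.** When the exposure is observed and patients are drawn at random, the number exposed is a result of sampling. One can fix the total, or fix both group sizes and sample by exposure status. The article fixes both group sizes and describes sampling that ignores exposure. The two agree only if frailty prevalence is close to 143/856 = 16.7%, a value the article does not state. Its planning figure is 20%.

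Eighteen centres therefore have two instructions that diverge as recruitment proceeds. If sampling is followed, the stated group sizes will not be met. If the group sizes are enforced, frail patients must be turned away once 143 are in, and the rest of the accrual is non-frail only. Calendar time would then be associated with frailty in the comparison of MINS between groups, and the frail group would lose part of the temporal coverage that the sampling scheme seeks.

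**Working it through.** **Inputs.** All are from Sample size calculation unless noted.
- Two-sided alpha 0.05. The text is "A bilateral α = 0.05 will be used with a 90% confidence interval"; the 90% is read here as power (an assumption, which the reproduction below supports).
- MINS risk 15% frail, 5% non-frail; frailty 20%; loss 20%.
- Evaluable 570 non-frail and 114 frail; enrolled 713 and 143, total 856 (also in Study design).
- Study period January 2023 to December 2024, about 24 months (Study design).

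**Step 1: reproduce the plan's figure.** Normal approximation with pooled variance under the null, p1 = 0.05, p2 = 0.15, ratio r = frail/non-frail = 0.2:
- pooled risk = (0.05 + 0.2 × 0.15)/1.2 = 0.0667
- n(non-frail) = [1.960 × √(0.0667 × 0.9333 × 6) + 1.282 × √(0.0475 + 0.1275/0.2)]² / 0.10² = 510
- with continuity correction: 569 non-frail and 114 frail, against 570 and 114 stated
- loss: 570/0.8 = 712.5, rounded up to 713; 114/0.8 = 142.5, rounded up to 143

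The figure reproduces at a 5:1 ratio. A frailty prevalence of 20% implies 4:1, where the same formula gives 480 and 120.

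**Step 2: what random sampling of 856 gives at 20%.**
- expected frail = 856 × 0.20 = 171; non-frail = 685
- standard deviation = √(856 × 0.20 × 0.80) = 11.7
- exact binomial P(143 or fewer frail) = 0.008

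This treats patients as independent draws with one common prevalence. Variation between centres would widen the spread but leave the expected split unchanged.

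**Step 3: what follows if, and only if, both counts are enforced as quotas.** With prevalence p:
- patients sampled when the 143rd frail patient enters = 143/p
- non-frail patients by then = 143(1 − p)/p
- patients sampled until 713 non-frail are in = 713/(1 − p)
- closing month = 24 × (143/p) / (713/(1 − p)), taking even accrual over 24 months

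| | p = 20% (plan) | p = 23% (assumed) |
|---|---|---|
| Sampled when the frail group fills | 715 | 622 |
| Sampled until 713 non-frail | 891 | 926 |
| Share of accrual | 80% | 67% |
| Closing month | 19.3 | 16.1 |
| Non-frail enrolled afterwards | 713 − 572 = 141 (20%) | 713 − 479 = 234 (33%) |
| Frail patients turned away | about 35 | about 70 |

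The 23% is the lowest specialty rate cited in the Introduction, for elective orthopaedic surgery. It is used only to show sensitivity.

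**Step 4: power if the split floats.** Evaluable at 20% frailty: 856 × 0.8 × 0.8 = 548 non-frail and 856 × 0.2 × 0.8 = 137 frail. Power by the normal approximation without continuity correction is about 0.95, against 0.92 for 570 and 114 by the same method.

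**The case against.** The strongest reply is that the harm in step 3 needs a closing rule, and the article has none. In a real-world cohort, giving group sizes under a sample size heading is ordinary wording. Speaking of patients being placed in groups may be loose phrasing, as is the Allocation row in Table 2, where nothing is allocated. If recruitment simply stops at 856, both groups stay open throughout and concurrency is kept. The full protocol might also settle the matter. This stands: lost concurrency is conditional, and a reader who infers that the frail group will close early goes beyond the text.

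Three other inferences are not supported:
- **That the sampling is meant to mirror case mix.** The Sampling section speaks only of the timing of case numbers.
- **That the frail group could fill within months.** The Introduction does report "In patients receiving elective orthopaedic surgery, the prevalence of frailty was 23%, whereas in patients undergoing emergency hip fracture surgery, it was 53" per cent, and other high rates, but these are for selected surgical populations. None estimates prevalence in this mixed cohort, so only 20% is a planning value.
- **That the main result would be distorted by an artificial frailty mix.** The analysis compares MINS between groups, and group-specific incidence does not depend on the frail share.

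Even under quotas at 20%, the frail group would stay open for about 19 months and so pass through every season at least once. Bias would also need MINS risk to change over the later months, for which the article gives no evidence.

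None of this removes the mismatch itself. Without quotas, the 713/143 split is what fails. And this is not detail left to a fuller document: the article states the split, the sampling and the 20%, and they disagree.

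**Conclusion.** The point holds as an inconsistency that should be corrected. At the plan's own 20% frailty, the described sampling gives about 171 frail and 685 non-frail patients out of 856, not 143 and 713, and a frail count of 143 or fewer has a probability of about 0.008. The source is a 5:1 ratio used beside a prevalence that implies 4:1.

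The consequence for comparability is conditional on the counts being enforced. In that case about 20% of the non-frail group would have no concurrent frail patients at 20% frailty, and about 33% at an assumed 23%. The closing months also rest on even accrual over 24 months; the shares do not depend on the length of the study.

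A reader might infer that the trial is too small. It is not on this ground: the sample size reproduces, and the split that random sampling would give has slightly more power than the stated one. True prevalence in this cohort is unknown. If it were near 16.7%, the stated split would be about what random sampling gives.

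**What to change.** In Study design and Sample size calculation:
- fix only the total of 856;
- state that neither group closes at any centre before the total is reached;
- replace 713/143 by the expected split at the planning prevalence, about 685 non-frail and 171 frail at 20%;
- keep 143 frail (114 evaluable) only as the minimum that the power calculation needs. Simply relabelling 713/143 as expected numbers would not do, since they are not the expected numbers at 20%.

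The cost is wording. No patients are added and power is not reduced (step 4). The downside is that final group sizes are not known in advance.

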**Fig. 1 Fig1:**
[figure not shown]
Flow diagram of the study

### Sample size calculation

In this study, the incidence of MINS will be the primary outcome. According to the literature review and pre-experimental results, the incidence of frailty is estimated to be 20%, with a MINS incidence of 15% in the frailty group and 5% in the non-frailty group. A bilateral α = 0.05 will be used with a 90% confidence interval. The sample sizes of the non-frailty and frailty groups have been calculated using the PASS 15.0 program; 570 patients will be included in the non-frailty group, and 114 patients will be included in the frailty group. Considering that the estimated proportion of patients withdrawn or lost to follow-up is 20%, 713 patients will be included in the non-frailty group, and 143 patients will be included in the frailty group; in total, 856 subjects will be included in the study.

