### Statistical analysis

Continuous variables will be expressed as the mean (standard deviation) or median (minimum, maximum; or interquartile interval). The classification variable will be expressed as the number of patients (percentage).A two-sided test will be used for all statistical analyses, and a difference will be statistically significant if the *P* value is less than 0.05.The chi-square test will be used to compare the overall case dropout rate between the two groups.The comparison of baseline numerical variables (such as age) between the groups will be conducted using independent sample t tests or Wilcoxon rank sum tests. Categorical variables (such as sex and the presence of comorbidities) will be compared between the groups by the chi-square test or Fisher’s exact test;The incidence of MINS within 3 days after the operation will be compared using the chi-square test.The incidences of postoperative complications and 30-day mortality will be compared with the chi-square test. The postoperative 30-day survival rate will be calculated by a survival analysis K‒M curve, and the difference between the groups will be evaluated by the log rank test.To determine the postoperative risk of MINS, multivariate logistic regression analysis will be conducted between the baseline and perioperative variables of different groups and the intervention factors, and odds ratios (ORs) and 95% confidence intervals (CIs) will be calculated. According to the main results (the occurrence or absence of MINS), the potential confounding effects on the main results will be adjusted in turn.Survival analysis of the incidence of postoperative MINS in the two groups: K‒M survival curve, Log RANK group comparison, and Cox risk proportion model.

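### The sample-size paragraph assumes 20% frailty but sizes the groups at 5:1 (16.7% frail), and it labels as a 90% confidence interval what its figures show to be 90% power

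*Protocol article*

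**What the plan says.** The Sample size calculation section of the protocol article gives these inputs:

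- Frailty: "the incidence of frailty is estimated to be 20"%.
- Event rates: "with a MINS incidence of 15% in the frailty group and 5% in the non-frailty group".
- Error rates: "A bilateral α = 0.05 will be used with a 90% confidence interval". No power is given.
- Evaluable groups: "570 patients will be included in the non-frailty group, and 114 patients will be included in the frailty group".
- Loss: "the estimated proportion of patients withdrawn or lost to follow-up is 20"%, which raises the groups to 713 and 143, 856 in all.

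The Study design section repeats the enrolled sizes: "There will be a total of 856 participants, of whom 713 will be placed in the non-frailty group and 143 in the frailty group". For the between-group comparison, the Statistical analysis section says "The incidence of MINS within 3 days after the operation will be compared using the chi-square test" and mentions no continuity correction. The Sampling section describes random selection of patients and does not mention selection by frailty status.

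**The concern.** Two statements in the basis for the primary outcome's sample size do not agree with the figures beside them.

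First, if 20% of the cohort is frail there are four non-frail patients for each frail one. The planned groups have five. Frailty is measured here, not assigned, so the split will follow the prevalence in the sampled patients. At 20% frailty a cohort of 856 would not be expected to divide 713/143.

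Second, two-sided alpha 0.05 corresponds to a 95% interval. A 90% confidence interval has no evident role in a calculation for comparing two proportions, whereas a power is required and none is named. As written, a reader cannot check the sample size without guessing the missing input.

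At stake is whether 856 is justified, and whether centres should treat 713 and 143 as targets to fill or as expected counts.

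**Working it through.** **Inputs** (all from Sample size calculation): p1 = 0.15 (frail), p2 = 0.05 (non-frail), difference 0.10, two-sided alpha 0.05 (z = 1.960), loss 20%. Assumption to be tested: the 90% is power (z = 1.282). Let n be the frail group and k the non-frail to frail ratio.

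**Ratio implied by the group sizes**

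- 570/114 = 5, and 114/684 = 16.7% frail.
- 713/143 is about 5, and 143/856 = 16.7% frail.
- A 20% share would be 0.20 × 856 = 171 frail, so rounding does not explain 143.
- The only place 0.20 appears is 114/570, the frail to non-frail ratio.

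**Reproducing the plan's figure (k = 5)**

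Uncorrected: n = [1.960·√(p̄(1−p̄)(1+1/k)) + 1.282·√(p1(1−p1) + p2(1−p2)/k)]² / 0.10², with p̄ = (p1 + k·p2)/(1+k).

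- p̄ = (0.15 + 0.25)/6 = 0.0667
- n = (0.5356 + 0.4743)² / 0.01 = 102.0, which would be 102/510.

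Continuity-corrected: n_c = (n/4)·[1 + √(1 + 2(k+1)/(n·k·0.10))]².

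- n_c = (101.99/4)·[1 + √1.2353]² = 113.7, rounded up to **114**; 5 × 114 = **570**. Exact match.
- Loss: 114/0.8 = 142.5, so **143**; 570/0.8 = 712.5, so **713**; total **856**. Exact match.

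Other variants tried at 5:1 do not match:

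| Variant | Frail/non-frail |
|---|---|
| 90% power, pooled, uncorrected | 102/510 |
| 90% power, unpooled | 144/720 |
| 90% power, one-sided | 86/430 |
| 80% power, pooled, uncorrected | 72/360 |
| 80% power, corrected | 84/420 |

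**Same method at the stated prevalence (k = 4)**

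- p̄ = (0.15 + 0.20)/5 = 0.07
- Uncorrected n = (0.5591 + 0.4784)² / 0.01 = 107.7, so 108/432.
- Corrected n_c = (107.65/4)·[1 + √1.2322]² = 119.8, so 120/480 = 600 evaluable.
- Loss: 120/0.8 = 150 and 480/0.8 = 600, so 750 enrolled. This is 856 − 750 = 106 fewer in total, but 150 − 143 = 7 more frail patients.

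**What 856 delivers at 20% frailty**

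- Expected: 171 frail, 685 non-frail. Evaluable: 0.8 × 171 ≈ 137 and 0.8 × 685 = 548.
- Standard error under the null 0.02437, under the alternative 0.03190.
- Corrected: effective difference 0.10 − ½(1/137 + 1/548) = 0.0954; z = (0.0954 − 1.960 × 0.02437)/0.03190 = 1.49; power 93.2%.
- Uncorrected: z = (0.10 − 1.960 × 0.02437)/0.03190 = 1.64; power 94.9%.

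**Whether the stated numbers fit together at 20% frailty**

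- 143 frail are expected by 143/0.20 = 715 enrolled.
- 713 non-frail are expected by 713/0.80 = 891 enrolled.
- Neither coincides with 856.

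**The case against.** The strongest reply is that nothing material changes. The arithmetic is right for 5:1, the inflation for loss is done correctly, and 856 exceeds the 750 needed at 4:1. This stands, and it limits the point to a correction of the text.

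A reader might infer that the plan misstates its power or falls short of 90%. The document does not support that. It states no power, so the fault is a wrong label and an omission. A shortfall can be constructed only by supposing that enrolment stops once 143 frail patients are in, with 143 × 4 = 572 non-frail and so 114/458 evaluable after 20% loss. Corrected power is then 88.6%. But no section contains such a stopping rule, and the abstract, Study design and Sample size calculation all give 856 as the total. The figure also depends on the continuity correction. Without it, as the plain chi-square test named in Statistical analysis would suggest, power in that same scenario is 91.4%.

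A reader might also take it as settled that 0.20 was typed in as the allocation ratio. The match with 114/570 makes this likely, but the software inputs are not shown. For the same reason the document does not settle whether the 20% or the 5:1 reflects the intended assumption.

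Finally, the 95% intervals in Statistical analysis are for odds ratios, so they are not a direct contradiction of the sample-size sentence. The misfit of the 90% interval is with the two-sided alpha of 0.05 in its own sentence.

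**Conclusion.** The point holds as an internal inconsistency and a wrong term in the sample-size basis of the primary outcome. The stated 20% frailty and the 5:1 group sizes cannot both describe the expected cohort: at 856 the difference is 171 − 143 = 28 frail patients. The 90% confidence interval should read as 90% power, since only that reading, with a continuity correction and 5:1, among those tried returns 114/570.

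The consequence is small and in the study's favour. If enrolment runs to 856 and 20% are frail, power is about 93% to 95%. If 16.7% are frail, the planned 143/713 is what one would expect and corrected power is 90%. Both figures rest on the protocol's own 15% and 5% event rates and its 20% loss, applied equally in both groups.

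**What to change.** Keep 856. In Sample size calculation:

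1. Replace the 90% confidence interval with 90% power, naming a continuity-corrected two-proportion test at two-sided alpha 0.05.
2. Reconcile prevalence and group sizes in one of two ways. Either keep 20% and restate the expected groups as about 171 frail and 685 non-frail (137/548 evaluable after 20% loss), with power about 93%; or keep 5:1 and 143/713 and restate the assumed prevalence as about 16.7%. The sponsor should choose according to what the literature review and pilot data support.
3. Say here and in Study design that the group sizes are expected numbers, not quotas, and that enrolment ends on the total.

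The cost is rewording one paragraph and one sentence. No patients, tests or procedures are added.
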